##### Secondary Outcomes

(1)The number of inpatients with SUDs will be compared with the total number of adolescents admitted to the Department during the inclusion period.(2)Descriptive analyses of clinical and psychosocial variables will be conducted. Chi-square will be used to compare categorical variables, and Student’s *t*-test for continuous variables. A difference of *p* < 0.05 will be considered statistically significant.(3)Univariate logistic regression analyses will be performed to determine whether clinical features (as independent variables) predict the onset of SUDs at 1 year (as dependent variable) in the non-SUD control group and persistence or cessation in the SUD group. Possible mediators of this relation will be examined using the four-step approach proposed by Baron and Kenny (65), followed by a Sobel–Goodman test. In particular, we will test the mediation effect of the baseline impulsivity score, the baseline level of sensation-seeking (subscales of the UPPS-P score), and the baseline level of mood lability (ARI total score) on the relationship between psychopathology and SUDs.(4)Comparable analyses would be conducted to determine the clinical and psychosocial risk factors for the persistence of SUDs among those with non-cannabis substance use at baseline.(5)Specific analyses based on mixed-effect models (a random effect for participants and fixed effects for time) will be performed to examine the interplay between the pattern of substance use, psychiatric symptoms, and contextual stressors for treating EMA data [as in Ref. (45, 66)]. In line with previous recommendations, data will be studied at the daily level (with average ratings), at the concurrent momentary level, and at the prospective level using both linear and non-linear modeling (32). These analyses will be performed and presented separately between those with cannabis use disorder and the other participants to prevent any interference due to the use of the Stop-Cannabis app.(6)Correlational analyses will be carried out to examine the association between the level of app use (EMA or Stop-Cannabis) (i.e., mean percentage of random prompts, mean percentage of days assessment completed) and participant’s clinical outcome at follow-up (i.e., frequency of substance use and level of functional impairment at 1 year).

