## Introduction

### Background

#### Substance Use Disorders and Psychiatric Disorders in Adolescents

Psychiatric comorbidity in adolescents who abuse substances is the rule rather than the exception, with 61–88% having a dual diagnosis (1, 2). The coexistence of both disorders is associated with important disruptions in a range of functional domains, including academic attainment, social and family relationships (2, 3), and accidents (4). In addition, initiation of substance use at a younger age (5) and a faster relapse after treatment (6) are reported in youths with preexisting mental health problems. In turn, the natural course of psychiatric disorders may be affected by substance use, either due to negative psychosocial consequences associated with substance involvement (7) and/or to the direct effect of the substance on the central nervous system (8). In youths with mood or psychotic disorders, for example, daily use of cannabis is associated with a more severe clinical presentation, impaired cognitive and interpersonal abilities, and poorer responses to pharmacological treatments (9). The development of integrative treatment for substance use disorders (SUDs) and psychiatric disorders is therefore a priority (10, 11).

Among adolescents hospitalized for a psychiatric problem, 17–50% meet criteria for one or more SUDs (12–17). In a previous study of adolescents hospitalized in three psychiatric units in France, most subjects met criteria for a non-nicotine SUD: around 70% for cannabis, 60% for alcohol, and 20% for other substances (18). Unsurprisingly, those with dual disorders exhibited more severe clinical characteristics (e.g., more suicide attempts) and a higher level of functional impairment (e.g., more school absenteeism) than patients without SUDs. They also received more diagnoses of axis 2 comorbidities and were exposed to more severe psychological contexts (e.g., maltreatment or loss of a first relative) (18). Given the high prevalence of SUDs among adolescents who are hospitalized, and the poor clinical outcomes due to the negative interplay between both disorders, specific preventive interventions for addiction should be developed and evaluated in this population.

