### Objectives

The primary objective of our pilot study is to evaluate the feasibility and acceptability of two different digital tools (an EMA tool and Stop-Cannabis) based on smartphone apps in adolescents with dual disorders during a 1-year follow-up period after hospital discharge. We aim to determine the feasibility of the EMA, adherence to recommendations, and the quality of data collected using an EMA digital assessment tool. In addition, we aim to evaluate the feasibility, acceptability, and use of the Stop-Cannabis app, a digital intervention tool, during outpatient aftercare. The authors expect to obtain from this pilot study data on the feasibility and acceptability of two kinds of digital tools (one related to assessment and the other one to an intervention) possibly useful for adolescents with SUDs and comorbid severe psychiatric disorders.

Secondary objectives are (1) to estimate the prevalence of SUDs in adolescents with psychiatric disorders hospitalized in the Department of Child and Adolescent Psychiatry at the Pitié-Salpêtrière University Hospital, Paris, France (this department provides one-third of all child and adolescent inpatient beds in the Paris area); (2) to describe the clinical and psychosocial characteristics of substance users compared with non-users; (3) to determine the risk factors for the onset of SUDs during follow-up in participants without dual diagnoses at baseline; (4) to determine the risk factors for the persistence of non-cannabis SUDs during follow-up; (5) to document the longitudinal interplay between substance use and psychopathology in adolescents with dual diagnoses at baseline; and (6) to examine the association between the use of the Stop-Cannabis app and the patterns of substance use at 1-year follow-up in naturalistic settings to inform the potentiality for future research.

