#### Statistical Methods

##### Primary Outcomes

Pearson correlations will be used to determine the strength of associations between daily substance use assessed by either EMA, or self-report questionnaire (e.g., CAST), or by clinician-report questionnaire (e.g., RECAP) during the clinical assessment at 6 months. Clinical reliability of the EMA will be endorsed if the correlations are statistically significantly higher than 0.70. Further analyses would be performed to estimate different aspects of reliability of the data collected in line with Perrez et al. (64). The severity of SUDs at baseline should predict the severity of substance use and the level of functional impairment at 1 year at least to comparable levels while using EMA data at baseline compared with traditional methods. Two simple linear regression models will be performed. For both the models, the dependent variable will be the severity of SUDs at follow-up; in one model, the independent variable will be the severity of SUDs based on EMA data (Model A), whereas in the other model, the variable will be severity of SUDs based on self- and clinician-report (Model B). The estimate of the independent variable is expected not to be lower in the Model A than in the Model B.

The dropout rate is expected to be less than 40% at 6 months and less than 50% at 12 months for both the EMA and traditional method, with no significant difference between methods. The results of the satisfaction survey will be estimated by analyzing the percentage of answers and the differences among the different categories using Chi-square analysis.

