#### Secondary Objectives

This study will measure the prevalence and the characteristics associated with the presence of SUDs in a sample of adolescents hospitalized in a psychiatric setting. Findings are expected to be in a similar range as those previously reported by Daudin et al. (18). We will then examine the possible relationship between SUDs and specific psychosocial and clinical features of inpatient adolescents. We expect this study to confirm that both internalized and externalized disorders are significantly associated with SUDs and that the presence of SUDs is associated with a higher level of impulsivity, mood dysregulation/borderline traits, and sensation-seeking traits (68–70). We predict that a bidirectional positive relationship between the level of substance use and the severity of other psychiatric symptoms will be noted at a daily level, and – if confirmed – that this association would be strengthened in a context of interpersonal relationship (with family and with peers) compared to other situations. A significant negative association between the level of the Stop-Cannabis app use and the participant’s clinical outcome at follow-up is expected. Such additional exploratory analysis would provide preliminary information about the possible benefit of the app in naturalistic settings.

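### Risk factors for SUD persistence are to be estimated one feature at a time without baseline substance-use severity, so the odds ratios can partly reflect that severity

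*Protocol article*

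**What the plan says.** All references are to the protocol article.

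- **Model.** Statistical Methods, Secondary Outcomes, item (3): "Univariate logistic regression analyses will be performed to determine whether clinical features (as independent variables) predict the onset of SUDs at 1 year". The sentence goes on to cover two groups: "in the non-SUD control group and persistence or cessation in the SUD group". Only the second group matters here.
- **Extension.** Item (4), for those with non-cannabis use at baseline: "Comparable analyses would be conducted to determine the clinical and psychosocial risk factors for the persistence of SUDs". By being comparable, these models inherit the univariate form.
- **Aim.** Secondary objective (4) is "to determine the risk factors for the persistence of non-cannabis SUDs during follow-up".
- **Third variables.** Item (3) names mediators only: "we will test the mediation effect of the baseline impulsivity score", together with sensation-seeking and mood lability. No severity term is listed.
- **Severity and later use.** Statistical Methods, Primary Outcomes: "The severity of SUDs at baseline should predict the severity of substance use and the level of functional impairment at 1 year".
- **Use and psychopathology.** The Introduction says that "the natural course of psychiatric disorders may be affected by substance use". The anticipated results for the secondary objectives predict "a bidirectional positive relationship between the level of substance use and the severity of other psychiatric symptoms will be noted at a daily level".
- **Availability.** Table 1 schedules DEP-ADO, RECAP and CAST at the initial assessment.
- **Other adjustment.** The Limitations section provides for regression control, but only if adherent and non-adherent participants differ at baseline.

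**The concern.** Everyone in the persistence analyses has a SUD at baseline, but its severity varies. A variable related to both the candidate feature and the outcome, and left out of the model, shifts the feature's odds ratio. On the plan's own expectations, baseline severity is such a variable. A larger univariate odds ratio for irritability, impulsivity or poor functioning could then mean partly that adolescents with these features were heavier users on admission.

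The aim is to determine risk factors, and the mediation analysis in item (3) begins from the same unadjusted association, so any such bias carries into it. The section on clinical and research implications looks to these results for mechanisms and for subpopulations on which integrated treatment should focus. For that use, it matters whether a feature adds anything beyond baseline use.

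**Working it through.** **1. What the plan quantifies.** It gives no odds ratio, correlation or power figure for these models. Its inclusion rate reproduces: 80 / 560 = 14.3%, stated as 14%.

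**2. Evaluable participants.** The Sample Size section gives 40 SUD cases and 50% retention at 1 year: 40 × 0.50 = 20 completers. The persistence rate is not given. Over an assumed 40% to 80%, the smaller outcome class is 20 × min(p, 1 − p):

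| Persistence | Smaller class | Per predictor, two predictors |
|---|---|---|
| 40% | 8 | 4 |
| 50% | 10 | 5 |
| 60% | 8 | 4 |
| 70% | 6 | 3 |
| 80% | 4 | 2 |

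If 20% to 60% of completers fall in the non-cannabis subset (an assumption), item (4) has 4 to 12 participants.

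**3. Size of the shift.** Assume standardised severity S with log odds ratio β for persistence, and a standardised feature X with correlation ρ to S and no effect of its own. The univariate log odds ratio for X is approximately

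ρβ / √(1 + 0.346 β² (1 − ρ²)),

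where 0.346 = (16√3 / 15π)² is the usual logistic-normal constant. The large-sample simulations used 60% persistence (intercept 0.4), or 50% for the last row.

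| ρ | Severity OR per SD | Approximation | Univariate OR | Simulated univariate OR |
|---|---|---|---|---|
| 0.3 | 2 | 0.208 / 1.073 = 0.194 | 1.21 | 1.21 |
| 0.3 | 3 | 0.330 / 1.175 = 0.281 | 1.32 | 1.31 |
| 0.5 | 2 | 0.347 / 1.060 = 0.327 | 1.39 | 1.37 |
| 0.5 | 3 | 0.549 / 1.146 = 0.479 | 1.61 | 1.59 |
| 0.7 | 3 | 0.769 / 1.101 = 0.698 | 2.01 | 1.99 |

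In the four simulated cases with ρ of 0.3 or 0.5, the odds ratio adjusted for S was 1.00. The shift does not shrink as the sample grows.

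**4. False-positive rate at a nominal 5%.** The plan does not name the test, and at this size it matters.

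- *20 completers, ρ 0.3 to 0.5:* about 3–9% by Wald test and 8–18% by likelihood ratio.
- *20 completers, ρ 0.7 and severity OR 3:* about 16% by Wald and about 30% by likelihood ratio.
- *Reference at 20:* with zero correlation the likelihood-ratio test already rejects about 6%. The severity-adjusted Wald test rejects 1–2%, so it is conservative here.
- *40 analysed, ρ 0.3 to 0.5, Wald:* 7–23% univariate against 4–5% adjusted. This needs full retention, which the plan does not anticipate.

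**The case against.** **The plan does not say that severity is a common cause.** A reader might infer that it expects baseline severity to drive both psychopathology and later use. The text does not go that far. The anticipated relationship is bidirectional and daily, within the EMA data. The Introduction also has the reverse order: youths with pre-existing mental health problems start earlier and relapse faster. The sentence on baseline severity compares EMA with traditional measurement, and its outcome is severity of use rather than persistence of a diagnosis. All of this stands. Severity may lie partly on the path from a feature to persistence, most plausibly for adverse childhood experiences, and adjusting would then remove part of the effect sought.

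**Prediction needs no adjustment.** Item (3) asks whether features predict the outcome, and a marker can do so without an effect of its own. This is a fair defence of keeping the univariate estimate. It does not cover statements about risk factors or the mediation tests, which are explanatory.

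**The study is a small pilot.** With 4 to 10 participants in the smaller outcome class, single-predictor models are defensible. This limits adjustment to one covariate and calls for a penalised fit, but it does not remove the bias.

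**Severity would rarely be mistaken for a risk factor.** A reader might infer that a feature with no effect will be reported as one. At 20 completers it would usually not reach significance, even in the most extreme case above.

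**Conclusion.** The concern holds for persistence or cessation in the SUD group, items (3) and (4). It does not extend to onset in the control group. The univariate form is stated in the plan, not left open, and it omits a collected variable that the plan links to both sides of the association. Its odds ratios can therefore partly reflect baseline severity.

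Under the assumed correlations of 0.3 to 0.7 and a severity odds ratio of 2 to 3 per SD, a feature with no effect of its own has a univariate odds ratio of about 1.2 to 2.0. None of these inputs comes from the documents. With about 20 completers the problem is mainly bias in the estimate. The false-positive rate is raised modestly over most of the range, and more at the strongest correlation or with a likelihood-ratio test.

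The documents do not settle whether severity is a confounder, a mediator or both. They therefore do not support treating the adjusted estimate as the only correct one.

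**What to change.** In item (3) for the SUD group and in item (4), keep the univariate odds ratio. Report beside it the odds ratio from a two-predictor logistic model, with the clinical feature plus one baseline severity score, fitted by Firth's penalised method. The score should cover all substances. DEP-ADO is a candidate, whereas CAST covers cannabis only. Label both estimates exploratory. Describe a feature as a risk factor independent of baseline use only if the adjusted estimate supports it, and do not present either estimate alone.

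The cost is a line or two of analysis text, with no new data. The downsides are wider intervals, with about 4 to 10 participants in the smaller outcome class and fewer among non-cannabis users, and possible over-adjustment where severity lies on the path. Showing both estimates lets the reader see how far they differ.

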#### Sample Size

A conservative approach was adopted for this feasibility study, which emphasizes descriptive and qualitative feedback. Consequently, based on the recommendations for pilot studies (44), we plan to include 80 participants (40 cases, 40 controls) over a 2-year inclusion period. As there are around 280 inpatient admissions per year in the Department of Child and Adolescent Psychiatry, i.e., *n* = 560 potential participants contacted at baseline during the 2 years, this will represent a 14% inclusion rate. We predict that the prevalence of SUDs will be similar to that previously reported (18). A good level of compliance with EMA and Stop-Cannabis is expected, consistent with previous studies that reported high levels of adherence (up to 80%) to similar tools in adolescents with comorbid psychiatric disorders (31, 45), and in adults with associated severe psychiatric disorders (32, 46). An acceptance rate of 80% is expected in the SUD group and 50% for the control group. A 50% retention rate at 1-year follow-up is anticipated based on previous longitudinal studies among adolescents (47). In case of a lower enrollment rate, we will either continue to enroll participants during an additional year (2019) in order to reach the intended sample size or use incentives (e.g., free participation in leisure and sport activities in groups) to encourage participant enrollment.

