### Clinical and Research Implications

The utility of app tools for adolescents with dual disorders would be of clinical interest, considering the need for evidence-based treatments and interventions in this population (71). Longitudinal data and mediation analyses would provide preliminary data on the mechanisms involved in the relationship between dual disorders (Figure 3). A better understanding of this mechanism is essential to focus on specific subpopulations in pursuit of more integrated treatment and support for their mental health and addiction problems. The originality of this study stems from the combination of tool-based measures with distinct temporal scale: standardized semi-structured interviews at baseline and end-point, self-reported non-ecological data obtained every 6 months, and self-measurement in the individual’s natural environment using EMA tools.

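### The causal-steps-plus-Sobel rule has almost no chance of detecting mediation at about 20 retained per group, and wastes power even with full retention

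*Protocol article*

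**What the plan says.** The protocol article, Statistical Methods, Secondary Outcomes item (3), begins with the outcome model: "Univariate logistic regression analyses will be performed to determine whether clinical features (as independent variables) predict the onset of SUDs". The relation is defined separately in the two groups, since clinical features are to "predict the onset of SUDs at 1 year (as dependent variable) in the non-SUD control group and persistence or cessation in the SUD group". For mediation the text continues: "Possible mediators of this relation will be examined using the four-step approach proposed by Baron and Kenny (65), followed by a Sobel–Goodman test". The candidate mediators are baseline impulsivity, baseline sensation-seeking and baseline mood lability (ARI total score).

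On numbers, Sample Size says "we plan to include 80 participants (40 cases, 40 controls) over a 2-year inclusion period" and "A 50% retention rate at 1-year follow-up is anticipated". Statistical Methods, Primary Outcomes, adds: "The dropout rate is expected to be less than 40% at 6 months and less than 50% at 12 months". No power, effect size or expected number of events is given for the mediation analysis.

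Clinical and Research Implications tells the reader what to expect from it: "Longitudinal data and mediation analyses would provide preliminary data on the mechanisms involved in the relationship between dual disorders".

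**The concern.** The causal-steps approach asks for a significant effect of psychopathology on 1-year SUD, a significant effect of psychopathology on the mediator, and a significant effect of the mediator on SUD given psychopathology, and then checks that the effect of psychopathology shrinks. The Sobel test is a further hurdle. Two features are costly. An indirect effect can exist without a significant total effect, so the first step discards true cases. The Sobel test treats the product of two coefficients as normal, which is a poor approximation in small samples and makes the test conservative.

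Applied to a binary outcome in about 20 participants, the procedure may be unable to respond to the data. The risk is then one of interpretation: a failure to pass the steps could be reported as a finding about mechanism when it reflects the test and the sample size.

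**Working it through.** **Plan's own arithmetic.** 80 participants out of 560 admissions is 80/560 = 14.3%, the stated 14%. Retained at 1 year: 40 × 0.5 = 20 per group. Expected events among 20: 2 at 10% risk, 10 at 50% risk.

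**Inputs not in the documents (assumptions).** Path a = 0.5 (mediator on psychopathology), log-odds 0.9 per SD of mediator (odds ratio e^0.9 ≈ 2.5), direct effect 0.3 on the log-odds scale, marginal 1-year risk 10–50%, two-sided 0.05 at every step. The protocol writes p<0.05 under item (2) only; applying it to each mediation step is the usual reading, not its text.

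**Why Sobel adds a hurdle.** The statistic is z = ab / √(a²·se_b² + b²·se_a²). With z_a = a/se_a and z_b = b/se_b this equals z_a·z_b / √(z_a² + z_b²). If both paths sit exactly at 1.96, z = 1.96/√2 = 1.39, well short of 1.96. With equal strengths, each path needs 1.96 × √2 = 2.77.

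**Simulation.** Draw psychopathology X, mediator M = 0.5X + error, and binary Y with logit = intercept + 0.9M + 0.3X. Fit M on X by least squares, and Y on X and Y on X and M by logistic regression. The full rule needs X→Y, X→M, M→Y given X, and Sobel all at p<0.05. The comparator needs only X→M and M→Y given X (joint significance), or a percentile-bootstrap interval for a×b that excludes zero.

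| Setting | Full rule | Comparator |
|---|---|---|
| Binary, n=20, risk 10–50% | about 0% | 0.3–7% (joint significance) |
| Binary, n=40, risk 10–50% | 0.6–11% | 14–52% (joint significance) |
| Continuous, n=20, a=b=0.5 | 3–9% | about 26% (bootstrap) |

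The bootstrap's false-positive rate is about 5%. At n=20 and 10% marginal risk, about 34% of ordinary logistic fits fail.

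**Sensitivity at n=20, binary outcome, logistic fits.**
- Under no effect the full rule rejects in 0.0%. From modest (a=0.3, odds ratio 2) to very large (a=0.6, odds ratio 6) mediation it rejects in 0.0–0.12%. With a=0.8 and odds ratios of 20–50 it rejects in at most 0.5%.
- Goodman's variance raises this to at most 0.4% for odds ratios up to 10. Likelihood-ratio steps give at most 1.5%, and Sobel alone at most 3.4%, both only in extreme scenarios.

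**Sensitivity to retention** (full rule, extreme effects excluded): n=24, 0–2.1%; n=28, 0–12%; n=32, 0–28%; n=40, 0–63%. Fitting the binary outcome by linear regression at n=20 gives 2.5–10% for large effects (a=0.5, odds ratio 4) and 4–22% for very large ones.

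**The case against.** The strongest reply is that this is low power in a secondary analysis of a pilot that is openly sized for descriptive feedback and promises only preliminary data. That stands in large part. At n=20 with a binary outcome, dropping both the total-effect step and Sobel still gives only 0.3–7%, so no test rule rescues a yes/no answer there. It does not stand at n=40, or for a continuous outcome, where the same data yield several times as many detections under the less restrictive methods.

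Two stronger readings are tempting, and the documents do not support either.
- A reader might infer that the analysis can only ever report no mediation. Item (3) says that mediators will be examined by the steps followed by the test; it does not write that every step must reach p<0.05. Dropout is expected to be below 50%, so 20 per group is the low end of the plan's own expectation, and the rejection rate rises with retention. The accurate statement is a near-zero rate at about 20 retained, not an impossibility.
- A reader might infer that pooling both groups on a continuous severity score would repair the analysis, since a continuous outcome at n=40 with a=b=0.5 gives a bootstrap rate of about 71%. That setting has twice the sample, another outcome type, no direct effect and no stated covariate adjustment. With a direct effect of 0.3 restored, the comparison narrows to 66% against 47% for the full rule. Pooling also replaces the protocol's questions, onset in those without SUD and persistence in those with it, by a different one.

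**Conclusion.** The concern holds in a limited form. With about 20 retained per group, a binary outcome and logistic fits, the prescribed procedure read in the usual way rejects in about 0% of trials even under a large assumed mediated effect. Small sample size explains much of this. The rule has its own cost on top: 0.6–11% against 14–52% at 40 per group, and 3–9% against about 26% for a bootstrap interval with a continuous outcome at n=20.

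The near-zero result at n=20 held over the whole range of effects and event rates tried with logistic fits. The sizes elsewhere depend on assumed effects, risks and retention. In consequence, a non-significant mediation result would carry almost no information, although the article presents this analysis as preliminary data on mechanisms. The primary feasibility outcomes are not affected.

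**What to change.** In Statistical Methods, Secondary Outcomes item (3), replace the four-step approach and the Sobel–Goodman test by an estimate of the indirect effect (a×b) with a percentile-bootstrap 95% CI, without requiring a significant total effect. Specifically:
- Keep the analysis within each group, so that onset and persistence remain the questions.
- Use penalised (Firth) logistic fits for the binary outcome, because ordinary fits often fail with few events.
- State that an interval including zero is not evidence of no mediation.
- As a supplement only, estimate the same indirect effect on continuous 1-year substance-use severity, adjusted for baseline severity. Table 1 already schedules DEP-ADO, RECAP and CAST at baseline and 1 year. A version pooled over groups may be added if labelled as answering a different question.

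The cost is a change of wording and a little more analysis work; no new data are needed. Intervals will still be wide at about 20 per group. The simulations above did not test the bootstrap combined with Firth fits on a binary outcome, so its coverage should be checked before it is fixed. With 2 events in 20, a resample contains no event with probability 0.9^20 ≈ 12%, and the handling of such resamples should be stated.

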#### Initial Clinical Assessment and Follow-Up

Participants (i.e., adolescents with SUDs and control subjects) will be approached by a researcher involved in the project (either a clinician specialized in child psychiatry or a master’s level psychologist) who will explain the study and obtain written informed consent from parents or guardian and assent from the adolescent. Participants will be assessed in the week prior to hospital discharge for sociodemographic data, psychosocial information, psychopathology, and substance use (see Variables and Instruments). All youths will be assessed in face-to-face interviews by a specially trained master’s level psychologist at 6-month and 1-year follow-up.

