**Psychopathology**				
K-SADS-PL	Semi-structured interview	X		X
Ado DIB	Self-report	X		X
ARI	Parent-report	X	X	X
	Self-report			
UPPS-P	Self-report	X	X	X
C-GAF	Self-report	X	X	X

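### The named mediators are measured at the same pre-discharge assessment as the psychopathology they should mediate, so a significant indirect effect would not separate mediation from confounding or reverse order

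*Protocol article*

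**What the plan says.** All references are to the Protocol article.

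- **Outcome model.** Statistical Methods, Secondary Outcomes, item 3, uses univariate logistic regressions in which clinical features "predict the onset of SUDs at 1 year (as dependent variable) in the non-SUD control group", and persistence or cessation in the SUD group.
- **Method.** "Possible mediators of this relation will be examined using the four-step approach proposed by Baron and Kenny (65), followed by a Sobel–Goodman test".
- **Mediators and their time point.** "we will test the mediation effect of the baseline impulsivity score, the baseline level of sensation-seeking (subscales of the UPPS-P score", and also "the baseline level of mood lability (ARI total score) on the relationship between psychopathology and SUDs". All three named mediators are baseline values.
- **When psychopathology is measured.** Initial Clinical Assessment and Follow-Up: "Participants will be assessed in the week prior to hospital discharge for sociodemographic data, psychosocial information, psychopathology, and substance use".
- **Schedule in Table 1.** The diagnostic interview is marked at the initial assessment and 1 year only ("K-SADS-PL Semi-structured interview X X"). The impulsivity scale is marked at the initial assessment, month 6 and 1 year ("UPPS-P Self-report X X X"). The ARI has the same three time points.
- **Use of the result.** Clinical and Research Implications: "Longitudinal data and mediation analyses would provide preliminary data on the mechanisms involved in the relationship between dual disorders".

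**The concern.** A mediator has to come after the exposure and before the outcome. Here the second half of that chain is in order, because baseline traits precede SUD status at 1 year. The first half is not. Psychopathology and the trait scores come from one assessment, and nothing in the design shows which came first. Impulsivity and sensation-seeking are trait-like and may well be older than the disorder.

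The planned calculation multiplies the association between psychopathology and trait by the association between trait and 1-year SUD. The first factor is the same whether psychopathology raises the trait, the trait raises psychopathology, or something else raises both. The protocol would nevertheless report the product as mediation and use it for preliminary statements about mechanisms. Better-timed scores on the same scales are already scheduled at month 6, and item 3 does not use them.

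**Working it through.** The plan gives no figure to reproduce on this point. The check has three parts.

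**1. Time order from the schedule**

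| Element | Instrument | Initial | Month 6 | 1 year |
|---|---|---|---|---|
| Exposure (diagnoses) | K-SADS-PL | X | | X |
| Mediators as planned | UPPS-P, ARI | used | collected, not used | collected |
| Outcome | SUD status | | | X |

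Item 3 does not write baseline next to psychopathology. It follows because the model predicts 1-year status and the only K-SADS-PL before that point is the initial one.

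**2. Can the planned test tell the structures apart?**

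Assumptions, none from the documents: correlation 0.4 between psychopathology X and trait M; log-odds of SUD = −0.8 + 0.3·X + 0.8·M, with X and M in SD units. Indirect effect = (slope of M on X) × (logistic coefficient of M given X). Sobel z = ab / √(a²·se_b² + b²·se_a²), two-sided 0.05.

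By arithmetic, ab = 0.4 × 0.8 = 0.32 in every case, because all three structures imply the same joint distribution of X and M. The simulation agrees:

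| Structure | Indirect effect, very large n | Sobel rejects, n=400 | n=40 | n=20 |
|---|---|---|---|---|
| Psychopathology → trait | 0.320 | 100% | 9.5% | 0.0% |
| Trait → psychopathology | 0.322 | 100% | 9.5% | 0.05% |
| Common cause | 0.319 | 100% | 9.7% | 0.1% |

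The rows differ only by simulation noise, so sample size is not the remedy.

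**3. Would the month-6 scores help?**

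Further assumptions: month-6 trait = 0.6 × baseline trait + g·X + noise (SD 0.7), with the baseline trait driving psychopathology. The true indirect effect is g × 0.8.

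| Mediator | g = 0 (truth 0) | g = 0.3 (truth 0.3 × 0.8 = 0.24) |
|---|---|---|
| Baseline score, as planned | 0.18 | 0.18 |
| Month 6, not adjusted for baseline | 0.19 | 0.43 |
| Month 6, adjusted for baseline | 0.00 | 0.24 |

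The planned mediator gives 0.18 whether or not mediation exists. Month-6 scores alone do not cure this: 0.6 × 0.4 × 0.8 = 0.19 remains when the truth is 0. Baseline adjustment is essential. At n=400 and g = 0, the planned version rejects in 95% of runs and the adjusted month-6 version in 2.7%.

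**Size actually available.** Sample Size plans 40 per group with 50% retention at 1 year: 40 × 0.50 = 20 per group. With g = 0.3, the adjusted month-6 model with a Sobel test rejects in about 3% of runs at n=40 and 0.1% at n=20. For onset in controls, an assumed rate of 10% to 25% gives 20 × 0.10 = 2 to 20 × 0.25 = 5 events.

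Two limits: the simulation used the Sobel test, not a bootstrap interval, and did not model substance use changing before month 6.

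**The case against.** The strongest reply has four parts.

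- **Measured together is not the same as occurring together.** The K-SADS-PL also covers lifetime disorders, so some disorders may predate the trait score, and the path from trait to 1-year SUD is prospective. This stands against the stronger reading that no mediation could exist or be shown. It does not establish the order, because the traits may be older still.
- **The stakes are modest.** The protocol calls the mechanism data preliminary, this is one secondary analysis in a pilot, and no primary outcome depends on it. This stands and limits the weight of the point. A reader might also infer that the study is likely to announce a false mechanism. The planned size does not support that: under the assumptions above, the planned test rejects in 0.1% of runs or fewer at n=20. The high rejection rates belong to n=400, which this study will not have.
- **The three scores are introduced as particular examples, so month-6 values are not ruled out.** True, but the analysis that is named fixes baseline values, and that analysis is the one at issue.
- **The month-6 repair has its own problem.** SUD can start or stop before month 6, so a month-6 trait score may be a consequence of the outcome. This stands, and the repair has to deal with it.

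The choice of Sobel or bootstrap and the small event counts are separate from time order. They matter here only for how a repaired analysis should be run at about 20 per group.

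**Conclusion.** The point holds in this form: the order of psychopathology and the named mediators is not established by the design, and a significant indirect effect from the planned test would not distinguish mediation from confounding or reverse order. That follows from the stated time points alone. The simulated values (0.32 under all three structures; 0.18 against a truth of 0) illustrate it and depend on the assumed correlation and effects. It also rests on reading psychopathology in item 3 as the initial assessment, which the schedule supports.

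The point does not extend to saying that mediation is impossible or that a false positive is likely. It should be corrected because the wording change is small and the needed scores are already collected, but it touches only one secondary analysis and the mechanism statement that draws on it.

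**What to change.** In Statistical Methods, Secondary Outcomes, item 3:

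- Use the month-6 UPPS-P impulsivity, UPPS-P sensation-seeking and ARI scores as mediators between baseline psychopathology and 1-year SUD status, adjusted for the baseline value of the same score.
- Adjust also for substance use at month 6 (RECAP and CAST, both scheduled then), or exclude participants whose SUD status had already changed by month 6. Table 1 has no diagnostic interview at month 6, so a rule based on RECAP and CAST would have to be written down in advance.
- Report the indirect effect with a bootstrap confidence interval instead of the four-step and Sobel–Goodman tests, and label it exploratory.
- Do not run mediation on SUD onset in the controls.
- If the baseline scores are kept, describe the analysis as adjustment for concurrent traits, not as mediation, and limit the mechanism statement in Clinical and Research Implications accordingly.

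Cost: analysis wording and one rule on month-6 status, with no new data collection. Participants missing at month 6 are lost to this analysis. Adjustment for month-6 use reduces the problem of early SUD change but may not remove it, because use and traits are measured at the same visit. With about 20 per group, power is very low and the interval will be wide.
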